## Background

Osteoporotic vertebral compression fractures (OVCF) are the most common fracture type in patients with osteoporosis, accounting for about half of osteoporosis-related fractures [1]. These fractures are associated with high morbidity and mortality [2], and vertebral augmentation is the standard operation for their treatment. While vertebral augmentation has significant effects in relieving pain and restoring vertebral height [3], it cannot fundamentally cure the fracture and prevent recurrence. Furthermore, the literature reports that the rate of recurrence of OVCF after vertebroplasty is high [4], ranging from 6.2% to 51.8% [5]. The debate on the risk factors of refracture after vertebral augmentation has lasted for nearly 20 years, but it is still inconclusive.

Osteoporosis is a complex disease caused by both genetic and environmental factors. While hundreds of genes and loci associated with osteoporotic fractures or bone mineral density have been identified through genome-wide association studies (GWAS), these can only explain a small proportion of the variation in the disease and its manifestations. For example, the 20 genes found in *GEFOS-1* explain only 5% of the phenotypic variation [6]. The hundreds of loci identified by the GWAS of bone mineral density based on UK biobank samples could only explain 12% to 20% of the phenotypic variation [7]. Therefore, the susceptibility genetic loci of osteoporosis found by GWAS alone cannot achieve accurate prediction of phenotypic changes, and even the prediction model based on a large number of genetic loci cannot achieve the accuracy required for practical applications in clinics.

Epigenetic modifications, including DNA methylation and histone modification, affect cell differentiation and development by affecting the structure and expression of genes, thereby regulating the genetic risk and environmental influence of various complex phenotypes and diseases [8]. Therefore, DNA methylation modification is considered as a bridge connecting genotypes and individual phenotypes. Epigenome-wide association studies (EWAS) of bone mineral density have discovered methylation sites playing a significant role in the pathogenesis of osteoporosis [9–15]. Furthermore, previous studies have revealed that exercise intervention for osteoporosis may achieve its effects by modulating the expression of bone metabolism genes via alterations in DNA methylation levels [16–18].

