The objective of this study is to investigate the genetic and epigenetic markers associated with osteoporosis and bone mineral density, and their impact on refracture risk among elderly patients. We aim to collect vertebral body blood and peripheral blood samples from 500 patients with OVCF who will undergo detailed clinical assessments, genome-wide genotype and methylation profiling at baseline. Following the surgical intervention, these patients will be followed up for 1 year to monitor refracture events, during which clinical and genome-wide methylation data will be collected again. These valuable data will enable us to identify genetic and epigenetic markers that can predict OVCF and refracture risk in the elderly and develop accurate prediction models.

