### Sample size

The power of EWAS is essential for detecting differentially methylated positions (DMPs) between cases and controls. Similar to GWAS, the power of EWAS depends on four key factors, including study design, sample size, effect size, and burdon of multiple test correction. Previous simulation analysis has shown that a sample of 500 cases and 500 controls would achieve 80% power to detect differential methylation at epigenome-wide significance (*P* < 1E-6) with a methylation odds ratio of 1.28 or mean methylation differences of 5% in case–control designs of EWAS (cite the original pubication) [19]. Therefore, we aim to recruit 500 elderly patients with OVCF who underwent vertebral augmentation surgery, as well as 500 healthy controls matched for age, gender, and race from the CAS cohort who did not develop OVCF or osteoporosis. This sample size will provide adequate statistical power for detecting significant differences in DNA methylation levels between cases and controls and enable us to identify epigenetic markers associated with refracture after vertebral augmentation surgery for OVCF.

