### Biomarker identification and prediction analysis

The GWAS of bone mineral density will be carried out in PLINK using linear regression model, assuming an additive allele effect. Covariates for age, gender, drug usage and the first five principal components to account for residual population structure will be also included in the model. The genomic control inflation factor will be used to adjust the *p*-values. The adjusted *p*-values equal to or smaller than 5E − 8 will be considered as genoome-wide significant. We will conduct a GWAS using case–control design to invesgate the genetic variants associated with osteoporosis.

This study will use whole-genome methylation data from vertebral and peripheral blood samples of 500 osteoporosis patients with recurrent fractures after vertebral augmentation and 1000 natural population controls from the Chinese Academy of Sciences. To identify differentially methylated positions (DMPs) between patients with and with out refracture, we will perform an epigenome-wide association study (EWAS) and meQTL analysis. Patients with refracture who underwent vertebral augmentation will be selected as cases, and an equal number of patients without refracture will be selected as controls based on age range and epidemiological indicators such as BMI, disease, and medication history. We will analyze changes in methylation levels of osteoporosis- and bone mineral density-related sites in elderly patients with refracture within one year after surgery. The R language DMRfinder package will be used for analysis, and functional annotation of the identified DMPs and differentially methylated regions (DMRs) will be performed.

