To predict BMD and OVCF risk, we will use multiple linear regression and multiple logistic regression models, respectively. We will include sex and age as predictors along with independent BMD-related genetic variants identified in previous studies and methylation sites identified in this study. Fracture risk score will also be evaluated based on age, gender, bone mineral density (BMD), previous fracture history, family history, and other risk factors. Prediction accuracy will be estimated using the R-squared correlation (R2) for BMD and the area under the curve (AUC) for OVCF risk. Sensitivities and specificities will be calculated using confusion matrices, where the predicted probability greater than a certain threshold (t) will be considered the predicted shape type, and t will be optimized to maximize the sum of sensitivity and specificity.

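### The prediction models refit published BMD variants by ordinary multiple regression with no score or shrinkage, which loses much of the genetic signal if many variants enter

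*Protocol article*

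**What the plan says.** Under Biomarker identification and prediction analysis, the protocol article says of BMD and OVCF risk that "we will use multiple linear regression and multiple logistic regression models, respectively". On the predictors it says "We will include sex and age as predictors along with independent BMD-related genetic variants identified in previous studies", to which it adds "methylation sites identified in this study". Accuracy is to be measured by an R-squared correlation for BMD and by AUC for OVCF risk, with classification at a threshold on the predicted probability. The section mentions no weighted genetic score, penalty or shrinkage. It does not give the number of variants or say which people are used to fit each model.

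The Background reports that 20 genes explain 5% of phenotypic variation and that hundreds of UK Biobank loci "could only explain 12% to 20% of the phenotypic variation". Its closing paragraph says the data will allow the investigators to "develop accurate prediction models".

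The Sample size section says "we aim to recruit 500 elderly patients with OVCF who underwent vertebral augmentation surgery", with "500 healthy controls matched for age, gender, and race from the CAS cohort". The analysis section instead has "1000 natural population controls from the Chinese Academy of Sciences". The possible fitting samples are therefore 500 (patients only), 1000 or 1500. The sample size is justified for the EWAS only.

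**The concern.** The variants appear in the plural beside sex and age as terms in a multiple regression, which reads as one freshly estimated coefficient per variant. The published effects are individually tiny: the Background's own figures average 0.25% of variance per gene for the set of 20 (5% / 20), and less per locus for the sets of hundreds. Without shrinkage, every added coefficient brings estimation noise of about the same size whether its true effect is large or negligible. With many variants and a few hundred to 1500 people, that noise can match or exceed the signal.

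This is a property of the fitted model. It remains even if discovery and evaluation are kept fully separate, and it arises from the published variants alone. Study-selected methylation sites would add to it. At stake is whether the models can use the genetic information already known, and whether their predicted probabilities are sound enough for the planned thresholding.

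**Working it through.** **The plan's own figure.** The article gives no sample size or expected accuracy for the prediction models. Its only figure is 80% EWAS power for 500 v 500 at P < 1E-6. That needs a standardised difference of (4.892 + 0.842) × √(2/500) = 0.363, so a 5% mean difference implies an SD of 0.05 / 0.363 ≈ 0.138. No SD is stated, so the figure can be neither confirmed nor refuted, and it does not bear on the prediction models.

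**Inputs.** n = 500, 1000 or 1500 (Sample size; Biomarker identification and prediction analysis). Joint R² = 5%, 12% or 20% (Background). The number of variants p is assumed: 20, as cited, and 100 and 300 to represent hundreds. Variants are taken as independent. Methylation sites are left out, which favours the plan.

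**Formulas for ordinary least squares in new people.**
- R² by prediction error ≈ 1 − (1 − R²)(n − 2)/(n − p − 2). This is zero at p = R²(n − 2), or about n × R².
- Squared correlation ≈ R⁴ / [R² + (1 − R²)p/(n − p − 1)], where R⁴ = (R²)².

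Example with n = 500, p = 100, R² = 12%:
- Prediction error: 1 − 0.88 × 498/398 = −10.1%.
- Squared correlation: 0.0144 / (0.12 + 0.88 × 100/399) = 4.2%.

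| n | Variants | True R² | R² by prediction error | Squared correlation |
|---|---|---|---|---|
| 500 | 20 | 5% | +1.0% | 2.8% |
| 500 | 100 | 12% | −10.1% | 4.2% |
| 500 | 100 | 20% | −0.1% | 10.0% |
| 500 | 300 | 12% | −121.3% | 1.0% |
| 500 | 300 | 20% | −101.2% | 2.8% |
| 1000 | 20 | 5% | +3.1% | 3.6% |
| 1000 | 100 | 12% | +2.2% | 6.6% |
| 1000 | 300 | 20% | −14.4% | 7.4% |
| 1500 | 20 | 5% | +3.7% | 4.0% |
| 1500 | 100 | 12% | +5.7% | 7.9% |
| 1500 | 100 | 20% | +14.3% | 15.6% |
| 1500 | 300 | 12% | −10.0% | 4.2% |
| 1500 | 300 | 20% | 0.0% | 10.0% |

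**Break-even with the mean, on prediction error.** At n = 500: 500 × 0.12 = 60 to 500 × 0.20 = 100 variants. At n = 1500: 180 to 300 variants.

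**Simulation check.** With 60 runs and 4000 new people each, prediction-error R² at n = 500 was +1.1% (20 variants, 5%), −9.5% (100, 12%), +0.2% (100, 20%), −120.8% (300, 12%) and −102.2% (300, 20%), in line with the formula.

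**Shrinkage without any published weights.** Ridge, with its penalty chosen by cross-validation, had lower prediction error than ordinary regression on the same data in all 15 settings tried (40 runs each):
- 100 variants, 12%, n = 500: 4.5% v −9.5%
- 300 variants, 20%, n = 500: 4.4% v −102%
- 300 variants, 20%, n = 1500: 10.7% v 0.4%
- 20 variants, 5%, n = 1500: 3.8% v 3.5%

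In those n = 500 runs, ordinary regression's squared correlation was 4.6% (100 variants, 12%) and 2.9% (300, 20%). A squared correlation is never below the prediction-error R² about the mean of the same test data. Ridge therefore reaches at least about 4.4% against 2.9% with 300 variants. With 100 variants these runs do not by themselves establish a gain on squared correlation.

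**Logistic model.** Simulated under an assumed liability model (15 runs), giving AUC refitted v true weights, then the proportional improvement in Brier score over no model:
- 500 v 1000, 20 variants, 5%: 0.592 v 0.607; +0.019
- 500 v 1000, 100 variants, 12%: 0.631 v 0.673; +0.015
- 500 v 1000, 300 variants, 20%: 0.633 v 0.721; −0.123
- 500 v 500, 100 variants, 12%: 0.611 v 0.668; −0.016
- 500 v 500, 300 variants, 20%: 0.617 v 0.720; −0.239

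**Published-weight score.** To match ordinary refitting on squared correlation, the score must keep the following share of its explained variance in this population:
- n = 500: about 56% (20 variants), 35% to 50% (100), 8% to 14% (300)
- n = 1500: about 80%, 66% to 78%, and 35% to 50%, respectively

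**The case against.** The decisive input is absent from the article. It gives no variant count and does not say that each variant has its own coefficient. The hundreds of loci are background, beside a set of 20, and such details are often left to a fuller document. This stands as a limit: the size of the problem is conditional on the count. It does not remove the point, because the article does state the model class and the form of the predictors, and neither includes a score or shrinkage.

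A reader might infer that the models would be worse than no model. On the protocol's own measures they would not be: squared correlation stays positive, and simulated AUC stays above 0.5. The negative values concern prediction error, and even there 100 variants at 20% and n = 500 is break-even.

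A reader might also infer that refitting always loses to a published-weight score. That depends on how far weights carry over to Chinese patients; the 12% to 20% comes from UK Biobank and no transfer figure is given. At half transfer and n = 1500, refitting wins on prediction error with 20 variants (3.7% v 2.5%) and with 100 variants at 20% (14.3% v 10%).

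Nor do the documents support a claim that a planned comparison of genetic with methylation information is distorted. The two enter joint models, and no head-to-head comparison is planned.

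A model of OVCF risk needs people without OVCF, so its n is 1000 or 1500. The n = 500 figures apply only to a BMD model fitted in patients alone, which the article neither specifies nor excludes. Finally, the Background already concedes that models with many loci lack clinical accuracy. That concerns how little variance the loci explain, not the further loss from re-estimating them.

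**Conclusion.** The concern holds in conditional form. As written, the plan re-estimates published small effects without shrinkage. On prediction error the linear model is expected to do no better than the mean once about 60 to 100 variants enter at n = 500, or about 180 to 300 at n = 1500. On squared correlation, roughly 60% of the available signal is lost with 100 variants at 12% and n = 500 (4.6% kept of 12%), and about 85% with 300 variants at 20% (about 3% of 20%). With 20 variants the loss is modest in absolute terms: on squared correlation 2.2 percentage points of 5% at n = 500 and 1.0 at n = 1500. For OVCF risk with 100 to 300 variants, simulated AUC falls from 0.67–0.72 to 0.61–0.63, and the Brier score is worse than no model in three of four settings.

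These sizes rest on assumed variant counts, independent variants, many small normally distributed effects (which suits ridge), the Background's variance shares applying to this population, and, for the logistic model, a liability scale. The case for shrinkage does not depend on published weights transferring.

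**What to change.** In Biomarker identification and prediction analysis, replace ordinary multiple linear and logistic regression with penalised regression (ridge or elastic net, penalty chosen by cross-validation) for the published variants and the methylation sites, in both models. Alternatively, where the published weights transfer adequately to this population, combine the published variants into one published-weight score per person and enter that as a single predictor, keeping the penalised per-variant fit as the alternative. State how many variants enter and which people each model is fitted in. If a score or penalty is already intended, one sentence saying so settles the point.

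The cost is wording and slightly more analysis work, with no new patient data. Individual variant coefficients would be shrunken, or absent if a score is used. A score may lose accuracy if its weights come from another ancestry, or because BMD weights are applied to OVCF risk.

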## Abstract

**Background:**

Osteoporotic vertebral compression fractures (OVCF) in the elderly increase refracture risk post-surgery, leading to higher mortality rates. Genome-wide association studies (GWAS) have identified susceptibility genes for osteoporosis, but the phenotypic variance explained by these genes has been limited, indicating the need to explore additional causal factors. Epigenetic modifications, such as DNA methylation, may influence osteoporosis and refracture risk. However, prospective cohorts for assessing epigenetic alterations in Chinese elderly patients are lacking. Here, we propose to conduct a prospective cohort study to investigate the causal network of DNA polymorphisms, DNA methylation, and environmental factors on the development of osteoporosis and the risk of refracture.

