**Methods:**

We will collect vertebral and peripheral blood from 500 elderly OVCF patients undergoing surgery, extract DNA, and generate whole genome genotype data and DNA methylation data. Observation indicators will be collected and combined with one-year follow-up data. A healthy control group will be selected from a natural population cohort. Epigenome-wide association studies (EWAS) of osteoporosis and bone mineral density will be conducted. Differential methylation analysis will compare candidate gene methylation patterns in patients with and without refracture. Multi-omics prediction models using genetic variants and DNA methylation sites will be built to predict OVCF risk.

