### Survey contents and methods (observation indicators)

The study includes eight categories of observation indicators and a total of 541 data items, as follows:Basic information: 21 data items, including age, gender, BMI, etc.Habit characteristics: 34 items in total, including eating habits, exercise habits, family activities, medication, and behavioral risk factors.Past medical history: 13 data items.Comorbidities/medication: 29 items.Diagnostic tests: 253 data items, including routine blood tests, coagulation tests, biochemistry, bone metabolism, sex hormones, white blood cell count, skin, pancreas and serum tests, thyroid function tests, tumor markers, imaging, functional score, color Doppler ultrasound, echocardiography, electrocardiogram, sarcopenia, infection index, and SF-36 quality of life (Table S1 and S2).Treatment plan: 36 data items.Postoperative follow-up: 139 data items, including follow-up table, functional score, bone metabolism, and SF-36 quality of life.Adverse events: 16 data items.

The follow-up plan includes two parts:

Patients will enter the data independently using their mobile phones, with real-time network supervision to ensure accurate data entry.Doctors will conduct monthly or regular telephone follow-ups to guide postoperative rehabilitation, which will last for 1 year.

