### Clinical implications/impact of the study

The systematic analysis of molecular mechanisms underlying osteoporosis and bone mineral density phenotypes is of great importance, and this study aims to explore cross-omics molecular markers that affect these phenotypes based on multi-omics data and the degree of physiological aging. The research objectives of this study include:Conducting genome-wide association analysis and genome-wide epigenetic association analysis of osteoporosis and bone mineral density to identify genetic and epigenetic molecular markers related to these phenotypes and to deeply analyze their molecular mechanisms.Evaluating the feasibility of DNA methylation in assessing the effect of postoperative intervention for osteoporosis by analyzing changes in methylation levels of bone mineral density related sites in elderly patients with refracture after vertebral augmentation for OVCF within one year after surgery.Improving the risk prediction model of osteoporosis by considering multiple factors such as genetic variation and environmental factors, which can provide a scientific basis for the molecular classification and prevention of related diseases and serve as a paradigm for biomedical researchers conducting multi-omics life data research.

The results of this study can provide valuable insights into the molecular mechanisms of osteoporosis and bone mineral density phenotypes, which can facilitate the development of effective interventions and personalized treatments. The findings can also contribute to the establishment of a risk prediction model for osteoporosis that takes into account genetic and environmental factors, which can help identify individuals at high risk for developing osteoporosis and enable targeted preventive measures. Overall, this study has the potential to make significant contributions to the field of osteoporosis research and improve clinical practice in the management of related diseases.

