### Advanced features of this study

To ensure data quality, we have established a special OVCF real-world research database system that supports data operation traceability, automatic logical verification, and other functions based on the ALCOA principle.We have assigned a special person to inspect the organization and implementation of the study, verify the data, and ensure accurate, timely, and complete data collection through quality control and assurance work meetings attended by all implementation units.To control the risk of loss to follow-up, we have implemented a patient data entry method and set up a special person to supervise the data entry. Follow-up personnel (doctors/nurses) will also follow up on patients’ data entry by monthly or regular telephone follow-up.To control patient compliance bias, we have established a unified clinical research platform for observation indicators such as out-of-hospital medication and dietary habits, and jointly set up personalized anti-osteoporosis programs with the department of endocrinology, rehabilitation, and nutrition to increase patient compliance. The study protocol was designed as a real-world study, and the final analysis was divided into groups according to the completion of the protocol to make the results closer to the clinical situation and increase the credibility of the study.We have implemented strict biobank management, ensuring the samples were only used for this study, destroyed after research, and information leakage was strictly controlled.Our study utilizes a multi-omics approach, incorporating whole genome sequencing and genome-wide methylation analysis to explore the interaction between genetics, epigenetics, and the environment in osteoporosis and bone mineral density phenotypes. This provides a more comprehensive understanding of the molecular mechanisms underlying these conditions.We have included a control group of 1000 healthy individuals from the Chinese Academy of Sciences natural population cohort, providing a larger and more diverse sample for comparison and analysis.We are exploring the feasibility of DNA methylation as a tool for evaluating the effect of postoperative intervention for osteoporosis by analyzing changes in the methylation levels of bone mineral density-related sites in elderly patients with refracture after vertebral augmentation for OVCF within one year after surgery.We are improving the risk prediction model for osteoporosis by incorporating multiple factors such as genetic variation and environmental factors, providing a more personalized approach to prevention and treatment.Our study is conducted in multiple medical centers, increasing the diversity of patient populations and enhancing the generalizability of our findings.

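### The third objective promises environmental factors in the risk model, but the predictors named for the BMD and OVCF models include none

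*Protocol article*

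**What the plan says.** **The promise.** In Clinical implications/impact of the study, the third listed objective is "Improving the risk prediction model of osteoporosis by considering multiple factors such as genetic variation and environmental factors". Advanced features of this study repeats it: "We are improving the risk prediction model for osteoporosis by incorporating multiple factors such as genetic variation and environmental factors". The Background of the abstract sets the wider aim as a "causal network of DNA polymorphisms, DNA methylation, and environmental factors" bearing on osteoporosis and refracture.

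**The data.** Survey contents and methods lists habit characteristics as "34 items in total, including eating habits, exercise habits, family activities, medication, and behavioral risk factors". BMI is recorded under basic information.

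**The model.** Biomarker identification and prediction analysis plans a multiple linear regression for BMD and a multiple logistic regression for OVCF risk. Both will "include sex and age as predictors along with independent BMD-related genetic variants identified in previous studies and methylation sites identified in this study". The Methods of the abstract agrees: "Multi-omics prediction models using genetic variants and DNA methylation sites will be built to predict OVCF risk". The sentence after the predictor list adds: "Fracture risk score will also be evaluated based on age, gender, bone mineral density (BMD), previous fracture history, family history, and other risk factors". Accuracy is then to be measured by R2 for BMD and by AUC for OVCF risk.

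**The concern.** The article promises a model with two kinds of input, genetic and environmental, and collects data on both. When it names the predictors, it carries forward the genetic kind, adds methylation, and leaves out the environmental kind.

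Two things are at stake. First, a study that follows the named list will finish without an answer on whether environmental factors improve prediction. Second, the contribution of methylation will be judged against age, sex and variants only. The Background describes methylation as regulating environmental influence and says that exercise may act on bone through it. A reader of the final R2 or AUC could not tell whether methylation brings new information or repeats what a questionnaire and a BMI measurement already give.

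**Working it through.** **1. Are the environmental data really collected?** The eight category counts in Survey contents and methods reproduce the stated total: 21 + 34 + 13 + 29 + 253 + 36 + 139 + 16 = 541. The habit items are 34 of 541, or 6.3%. BMI comes on top, within the 21 basic items.

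**2. Promise against plan.**

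| Input | Third objective and Advanced features | Predictors named for the BMD and OVCF models |
|---|---|---|
| Genetic variation | yes | yes (variants known from previous studies) |
| Methylation | not named in that sentence | yes (sites found in this study) |
| Environmental factors | yes | none named |
| Age, sex | not named in that sentence | yes |

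The genetic part of the objective is covered. The environmental part is not.

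**3. Does the fracture risk score fill the gap?** It names age, gender, BMD, previous fracture and family history, and ends with an unspecified remainder. No habit item is named. The text does not say that the score enters the regressions or that it is compared with them.

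**4. Are these items used elsewhere?** Yes, in part. The BMD GWAS adjusts for drug usage. The refracture comparison selects controls on age range and on indicators such as BMI, disease and medication history. Neither step puts an environmental predictor into the prediction models or estimates what one contributes.

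**5. What does the omission do to the reading of R2?** Take standardised variables: an environmental factor E with coefficient b on BMD, and a methylation site M that has correlation r with E and no effect of its own. Let both be independent of the other predictors.
- E left out: M receives the coefficient r × b and raises R2 by r² × b².
- E included: M receives the coefficient 0 and raises R2 by 0.

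The shift is therefore r² × b², and it vanishes if either r or b is zero. The documents give neither quantity, so no size can be derived. The same reasoning applies in kind to the AUC of the logistic model.

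**6. In whom could environmental terms be fitted?** Survey contents and methods describes data collection for OVCF patients and is silent on the natural-population controls. Table 1 places eating and exercise habits at the treatment stage, which is after the fracture. Sample size matches these controls on age, gender and race, not on habits.

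**The case against.** **The list may not be exhaustive.** The text says what will be included, not that nothing else will be. This is a condensed article, and choosing among 541 items is ordinary analysis-plan work. That would carry weight if the predictors had been left open. Here the article names them, the abstract describes the same omics inputs, and neither matches the stated objective. The mismatch lies within the article.

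**A methylation site that reflects exposure is a legitimate predictor.** This stands. The AUC of such a model is not invalid, and the article does not claim a gain of methylation over lifestyle. A reader might infer that methylation will be credited with what the habit items already predict. The documents do not support that as fact. It needs selected sites that track habits and habits that predict the outcome, and the Background makes this only plausible.

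**Some of these items are used.** This also stands. A reader might infer that environmental and related items are collected and then used nowhere, but drug usage is a GWAS covariate, and BMI and medication history guide the choice of refracture controls. A reader might likewise infer that the third objective is wholly untested, but its genetic part is modelled.

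**The remedy may be unavailable for OVCF risk.** This is a fair limit. Nothing shows that the controls have comparable items. Habits recorded after a fracture may have been changed by it, so comparing them with those of controls could inflate the AUC.

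**Conclusion.** The point holds in a limited form. The objective calls for environmental factors, and the named predictors of the BMD and OVCF models contain none. The fracture risk score does not close the gap, because it names no habit item and has no stated link to those models. If the plan is followed as written, the environmental part of the third objective goes unanswered, and R2 or AUC cannot show what methylation adds beyond the habit items and BMI.

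That methylation may partly stand in for environment is a possibility that the article's own Background raises. Its size cannot be taken from the documents, and any figure would rest on assumed effects and correlations. The conclusion does not depend on one. It rests on reading the predictor list as the intended model, which the abstract supports.

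**What to change.** In Biomarker identification and prediction analysis:

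1. Name a short fixed set of environmental predictors, for example BMI, exercise, diet and behavioural risk factors.
2. Fit nested models in a fixed order: age, sex and the environmental set; then the known variants; then the methylation sites. Report R2 or AUC at each step.
3. Do this for BMD in the patients, where the items are collected.
4. For OVCF risk, use only items recorded comparably in the natural-population controls and referring to the period before the fracture. State which items qualify. If none does, restrict the environmental part of the third objective to the BMD model, and align Advanced features with it.
5. State whether the fracture risk score is a separate comparator or enters these models.

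**Cost.** A few degrees of freedom. If the set took 6 to 10 terms (an assumption), 500 patients would give 500/6 = 83 to 500/10 = 50 per added term. That count leaves out the variants and methylation sites, whose number is not stated. Someone must also check what the controls' cohort recorded. The apparent contribution of methylation may turn out smaller.
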